### 2.4. Data Collection

#### 2.4.1. Baseline Data

Demographic information, vital signs, medical history, concomitant medication and treatment details will be collected for each participant at the start of the study. This includes patient factors (age, sex, height, weight, blood pressure, pulse, body temperature, medical history, AEs of TEA within one year, medication history within one week, and concomitant medications or treatments), practitioner background factors (length of practice, affiliations, and board certification), and intervention factors (target disease, product manufacturer, thread material, thread shape, thread size, treatment area, number of needle insertions, needle length, needle thickness, and needling depth).

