#### 2.4.2. AE Monitoring

Definition of AEs [34]: AEs are defined as any unfavorable or unintended signs, symptoms, or diseases temporally associated with the TEA procedure.

Monitoring Schedule: Patients will be monitored at baseline (V1: enrollment period and first TEA treatment), 1 week post-treatment (V1 + 7D), 1 month post-treatment (V1 + 1M), 3 months post-treatment (V1 + 3M), and during intermediate procedures performed within 3 months post-treatment (evaluated 1 week later—Vn + 7D). In addition, participants will be encouraged to self-report AEs at any time during the study period using an application or diary. Symptom confirmation and evaluation will be conducted on the designated assessment dates.

All symptoms will be independently assessed by an investigator blinded to the specific TEA details and subsequently confirmed for AEs by the practitioner who performed the TEA to ensure that no AEs are omitted that are unrecognized by the patient or the blinded assessor. Patients will also be encouraged to voluntarily upload photos of AEs to the self-reporting application if they would prefer, so that they can be independently assessed by blinded researchers and medical staff. In addition, depending on the AE, appropriate medical examination and management, including laboratory tests and imaging, will be applied until the AE resolves.

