#### 2.4.3. Outcome Measures

The development of a standardized AE-reporting form is essential to facilitate accurate data collection, improve the quality of post-medical treatment, and ensure patient safety. The Medical Dictionary for Regulatory Activities (MedDRA) is a standardized international lexicon that is used by regulatory authorities for data related to medical treatments [35]. In the present study, the safety information report was developed based on the integration of MedDRA system organ class (SOC) and preferred term (PT) and a Delphi, a well- structured technique using collective consensus of multiple clinical experts [36]. Symptoms that may be associated with TEA are presented in Table 2.

Causality is assessed by evaluating the following causal factors according to the WHO-UMC criteria [37], which are the most widely used worldwide.

Is there a temporal relationship between the TEA and the occurrence of the AE?Does the same AE occur if TEA is repeated?Is it possible that the patient’s underlying medical condition or concomitant medication or procedure is the cause?Has the same AE been reported in the past?Did the AE improve after TEA was stopped?Is there a reasonable biological relationship between the procedure and the AE?

The outcome measure is the incidence, nature, and severity of AEs associated with TEA. During the 3-month post-treatment period, the incidence of AEs and rate of TEA treatment discontinuation due to AEs will be assessed. In addition, patient-, practitioner-, and intervention-related factors associated with the occurrence of AEs will be examined. The Standard Protocol Items: Recommendations for Interventional Trials (SPIRIT) schedule of enrollment, interventions, and assessments is shown in Table 1. The SPIRIT Checklist can be found in the Supplementary Files.

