### Strengths and Limitations

This study is the first to systematically evaluate the safety of TEA in real-world clinical settings across multiple centers.Detailed documentation of the TEA procedure, including regarding the target disease, TEA products and manufacturers, thread types and specifications, treatment areas, and insertion techniques, allows for a comprehensive analysis of potential risk factors.The observational study design enables the capture of both immediate and delayed AEs over a 3-month follow-up period.To minimize recall and reporting bias, a mobile application has been developed to enable patients to self-report AEs at their convenience, which will be independently assessed by blinded assessors and double-checked by the practitioner.As an observational study, it is not possible to definitively establish causality between TEA and AEs.This study is conducted in a single country, which limits its applicability in other countries; however, it includes a diverse range of healthcare organizations and patient populations to enhance the generalizability of the findings.Inherent observer bias may affect the interpretation of the results of this study, and we aimed to minimize this bias by implementing inter-rater standardization in this study.

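### The unblinded treating practitioner has the last stated say in AE ascertainment, so AE capture can differ by the practitioner and technique factors under study, even if that step only adds AEs

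*Protocol article*

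**What the plan says.** Section 2.4.2 (AE Monitoring) describes two steps. First, "All symptoms will be independently assessed by an investigator blinded to the specific TEA details". The symptoms are then "subsequently confirmed for AEs by the practitioner who performed the TEA", and the same sentence gives the reason: "to ensure that no AEs are omitted that are unrecognized by the patient or the blinded assessor". Strengths and Limitations describes the self-reported AEs as "independently assessed by blinded assessors and double-checked by the practitioner", and presents this as a way to reduce recall and reporting bias.

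The people and procedures involved in the second step are also objects of study. Section 2.4.1 collects "practitioner background factors (length of practice, affiliations, and board certification", together with intervention factors such as thread, area, number of insertions and depth. Section 2.4.3 says that "patient-, practitioner-, and intervention-related factors associated with the occurrence of AEs will be examined". The outcome itself is defined there: "The outcome measure is the incidence, nature, and severity of AEs associated with TEA".

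The article does not say whose judgement counts when the blinded assessor and the practitioner disagree, or whether the blinded assessment is kept as a separate variable for analysis.

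**The concern.** The practitioner who performed the procedure knows the product, area, depth and number of insertions, and cannot be blinded to them. That person's background and technique are also the explanatory variables. If recognition of AEs, or willingness to record them, varies with experience, affiliation or technique, the count of AEs will vary with those factors even when the true risk does not.

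The analyses at stake are mainly the practitioner- and intervention-factor comparisons. A group that looks harder for AEs and adds more of them will look less safe. A group that adds few will look safer. The article's Discussion expects the results to guide safer technique and to inform guidelines, so a spurious association here could be acted on.

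**Working it through.** **The plan's own figure.** Section 2.5.1 gives an expected incidence of 12%, a margin of ±3.5 points, 95% confidence and 5% dropout.
- n* = 0.12 × 0.88 × 1.96² / 0.035² = 331.16, which the article gives as 331.2.
- 331.16 / 0.95 = 348.6, so 349, with about 350 to be recruited.

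The figure reproduces, and nothing in this point changes it. It supplies the 12% used below.

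**What the text allows.** Two readings of the second step are possible.
- *Addition only.* The purpose clause in Section 2.4.2 supports this reading.
- *Addition or removal.* The verb leaves this open, because a symptom that is to be confirmed as an AE can also fail to be confirmed. No sentence says that it may.

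**Addition only.** Let p be the true risk, s the share of AEs captured by patients and blinded assessors, and r the share of the missed AEs that the practitioner adds. All added AEs are taken to be true ones. Then

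observed risk = p × [s + (1 − s) × r].

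The inputs are p = 12% (Section 2.5.1), and s and r as assumptions, because the documents give neither. Group A adds every missed AE (r = 1) and is observed at 12.0%. Group B has the same true risk.

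| s | r in group B | Observed risk, group B | Risk ratio, B to A |
|---|---|---|---|
| 0.85 | 0.5 | 0.12 × 0.925 = 11.1% | 0.925 |
| 0.85 | 0 | 0.12 × 0.85 = 10.2% | 0.85 |
| 0.70 | 0.5 | 0.12 × 0.85 = 10.2% | 0.85 |
| 0.70 | 0 | 0.12 × 0.70 = 8.4% | 0.70 |

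The true risk ratio is 1 in every row. If both groups add the same share, the ratio stays at 1. The distortion comes from the difference between groups, not from adding as such.

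Overall incidence behaves differently. With s = 0.85 and equal groups, the blinded and self-reported count alone gives 10.2%. The union gives (12.0 + 11.1)/2 = 11.55% if group B adds half, or (12.0 + 10.2)/2 = 11.1% if it adds none. Under this reading the union lies closer to the true 12% and never below the blinded count.

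**Effect on the tests.** With two equal groups of 166 (331.2/2 = 165.6), the chance of a significant result in the spurious direction, against 2.5% nominal, is about 5% for 12.0% versus 10.8%, 10% for 12.0% versus 9.6%, and 19% for 12.0% versus 8.4%. The rows with a risk ratio of 0.85 (12.0% versus 10.2%) fall between the first two. The last row of the table is the 19% case.

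**If removal were allowed (not established by the text).** If all practitioners left 10%, 20% or 30% of AEs unconfirmed, a true 12% would be reported as 10.8%, 9.6% or 8.4%. The last is a shift of 3.6 points, about the whole planned margin of 3.5. These figures only show what the ambiguity could cost.

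**The case against.** A reader might infer that an AE counts only once the practitioner has confirmed it, so that the operator holds a veto over the blinded assessor. The documents do not support that. The sentence in Section 2.4.2 goes on to an additive purpose, and Strengths and Limitations speaks only of a double check. The AE definition in Section 2.4.2 contains no confirmation condition. Section 2.4.4 has staff write a report for each AE after treatment, and Table 1 lists patient and physician evaluation as separate rows and includes a self-reporting column. It follows that downward bias in overall incidence, and loss of the benefit of blinding, cannot be asserted. An additive check leaves the blinded findings in place.

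It can also be said that a disagreement rule belongs in a full protocol or case report form, and that the authors acknowledge observer bias and trained their staff. The first part stands as far as a missing rule goes, since a fuller document may contain one. The point does not rest on that gap, though. The article itself fixes who makes the last check and in what order, and counts this as a strength. Training standardizes raters but does not blind the operator. The rule in Section 2.5.2 that takes the maximum severity and causality applies to AEs already counted.

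Finally, dropping AEs that only the practitioner found from the factor analyses would discard what the step exists to catch, and self-reports are not stated to come from blinded patients. This is a fair reason to show both analyses rather than prescribe one as primary.

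**Conclusion.** The point holds in a limited form. The last stated step of AE ascertainment is made by an unblinded person whose background and technique are the exposures, so capture can differ by exposure even if the step only adds AEs. With 85% capture before that step, equal true risks could appear as a risk ratio of 0.925 or 0.85. A ratio of 0.70 needs 70% capture and one group adding nothing. These sizes rest on assumed capture and addition rates, on added AEs being genuine, and on the practitioner groups differing in how much they add.

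For overall incidence, the additive reading gives no reason to expect a figure below the blinded count. A downward bias would need removal of AEs, which the wording does not rule out but the text does not establish. No sample-size figure is affected.

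**What to change.** - In Section 2.4.2, state that the practitioner may add AEs but may not remove or downgrade one recorded by the blinded assessor. If a fuller protocol already says so, carry the sentence over.
- Keep a source flag for each AE: blinded assessor, self-report, or practitioner only.
- Report overall incidence on the union of all sources.
- Run the practitioner- and intervention-factor analyses on the union and also on AEs identified independently of the practitioner, and show the two side by side. Interpret an association cautiously if it appears only in the union.

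The cost is one sentence, one data field and one extra analysis run, with no extra staff. The practitioner-independent analysis will have fewer events and so less precision.

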#### 2.4.3. Outcome Measures

The development of a standardized AE-reporting form is essential to facilitate accurate data collection, improve the quality of post-medical treatment, and ensure patient safety. The Medical Dictionary for Regulatory Activities (MedDRA) is a standardized international lexicon that is used by regulatory authorities for data related to medical treatments [35]. In the present study, the safety information report was developed based on the integration of MedDRA system organ class (SOC) and preferred term (PT) and a Delphi, a well- structured technique using collective consensus of multiple clinical experts [36]. Symptoms that may be associated with TEA are presented in Table 2.

Causality is assessed by evaluating the following causal factors according to the WHO-UMC criteria [37], which are the most widely used worldwide.

Is there a temporal relationship between the TEA and the occurrence of the AE?Does the same AE occur if TEA is repeated?Is it possible that the patient’s underlying medical condition or concomitant medication or procedure is the cause?Has the same AE been reported in the past?Did the AE improve after TEA was stopped?Is there a reasonable biological relationship between the procedure and the AE?

The outcome measure is the incidence, nature, and severity of AEs associated with TEA. During the 3-month post-treatment period, the incidence of AEs and rate of TEA treatment discontinuation due to AEs will be assessed. In addition, patient-, practitioner-, and intervention-related factors associated with the occurrence of AEs will be examined. The Standard Protocol Items: Recommendations for Interventional Trials (SPIRIT) schedule of enrollment, interventions, and assessments is shown in Table 1. The SPIRIT Checklist can be found in the Supplementary Files.

#### 2.4.4. Data Collection and Management

Trial staff will create a safety information report for each AE that occurs after TEA treatment. To ensure inter-rater standardization, trial staff were trained in a 1-day workshop on consistent assessment criteria, protocols, and reporting forms. The training included case scenarios, role-playing, and practical exercises, followed by performance assessments and feedback. Ongoing AEs at the time of the report will be verified at the next follow-up evaluation and documented until resolution. Patients will be encouraged to self-report AEs using an application. All data will be retained for three years after the study’s completion. For security, the source data will be protected using study identification numbers. Personal patient information will be stored in a subject identification log, which will be kept in a locked cabinet accessible only to authorized personnel. Protocol revisions will be managed by Sangji University Korean Medicine Hospital, the central coordinating facility. They will conduct site-level monitoring to ensure the protection of participant rights, and adherence to research protocols.

### 2.5. Statistical Analysis

#### 2.5.1. Sample Size Calculation

This prospective observational study will be conducted in a real-world clinical setting involving a diverse patient population with various diseases and clinical backgrounds. Given the expected high heterogeneity of the participants and high variance in the data, statistical sample size calculations are challenging. A previous study reported the incidence of AEs following TEA [38]; however, the data were based on published randomized controlled trials and case reports rather than actual clinical practice. To address these limitations, the sample size for this study was conservatively estimated at 12%, based on preliminary pilot data (unpublished). Using a margin of error of ±3.5% and a confidence level of 95%, the sample size calculation was performed. Accounting for an expected 5% dropout rate, the study aims to recruit approximately 350 participants.$$n^{*}=\mathrm{pq}\frac{{\left(Z_{\alpha /2}\right)}^{2}}{d^{2}}=0.12\times (1-0.12)\times \frac{1.96^{2}}{0.035^{2}}=331.2,\;n=\frac{n^{*}}{\left(1-\omega \right)}=\frac{331.2}{0.95}\approx 349$$

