## 2. Methods

### 2.1. Study Design, Setting and Aim

This multicenter, prospective, observational study will evaluate the safety of TEA in clinical practice. The study protocol is registered with the Clinical Research Information Service (CRIS; https://cris.nih.go.kr, (accessed on 16 December 2024); registration number KCT0008912). Participants will be recruited from three university-affiliated hospitals and two traditional Korean medicine clinics in Korea. Patients receiving at least one TEA treatment in a real-world setting, in line with the eligibility criteria, will be enrolled, and all AEs occurring in participants for a total of 3 months will be prospectively collected. In clinical practice, each patient will receive an appropriate number of TEA treatments based on their disease and condition; therefore, all additional TEA treatments after the first treatment will be collected as V2 to Vn in this study. Data regarding all TEAs received by participants and all AEs occurring during the study period will be collected and evaluated. The study procedure and assessment protocol for this trial are presented in Figure 1 and Table 1.

This study aimed to prospectively evaluate and validate the safety of TEA in real-world clinical practice. This observational approach enables the collection of safety data from a diverse patient population to reflect the complexities of actual clinical practice.

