#### 2.5.2. Statistical Methods

The analysis group will include participants who have received at least one TEA treatment. The main observation indicators, including the incidence rate of AEs and the treatment discontinuation rate, will be collected and analyzed without replacing the missing data. Continuous data will be represented using descriptive statistics, such as the number of participants, mean, and standard deviation, whereas categorical data will be presented as frequencies (N) or ratios (%). When necessary, a 95% confidence interval will be calculated. Unless otherwise specified, the statistical tests will be conducted using a two-sided significance level of 5%.

Student’s *t*-test will be used to compare normally distributed continuous variables and the Wilcoxon rank-sum test or Mann–Whitney U test will be used to compare non-parametric continuous variables between the patient groups with AEs and those without. A Shapiro–Wilk test and Kolmogorov–Smirnov test will be used to assess the normality of the distribution. The chi-square test (or Fisher’s exact test, when appropriate) will be used to compare dichotomous variables such as sex, the presence of comorbidities, and co-medications between the patient groups with and without AEs. Variables with *p* < 0.05 in the bivariate analysis or those considered clinically relevant will be included in the final regression model. The Kaplan–Meier method will be used to analyze the incidence of AEs and Cox proportional hazards regression will be used to analyze the differences in the incidence of AEs between subgroups including demographic characteristics, TEA materials or procedures.

All AEs collected in the study will be categorized according to the SOC and PT as defined in the MedDRA. The incidence and incidence rates will be presented by PT; however, multiple occurrences of the same AE by PT in the same subject will be considered as a single event. Furthermore, different discovered severities and causalities for the same AE will be treated as the maximum severities and causalities, respectively. Moreover, AEs associated with TEA and SAEs will be presented as events.

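### The ±3.5-point margin assumes independent patients and leaves no room for correlation within practitioners, and the patient-level tests named in 2.5.2 would be anti-conservative for practitioner factors

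*Protocol article*

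**What the plan says.** Section 2.5.1 sizes the study on the precision of a single proportion. The expected incidence is introduced with "the sample size for this study was conservatively estimated at 12%, based on preliminary pilot data (unpublished"), and then: "Using a margin of error of ±3.5% and a confidence level of 95%, the sample size calculation was performed". The printed formula is pq·z²/d², giving 331.2 and then 349 after division by 0.95. The only inflation is for dropout: "Accounting for an expected 5% dropout rate, the study aims to recruit approximately 350 participants". The same paragraph expects marked heterogeneity among participants, but no term in the formula reflects it.

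On the design, section 2.1 says "Participants will be recruited from three university-affiliated hospitals and two traditional Korean medicine clinics in Korea". Section 2.4.1 lists "practitioner background factors (length of practice, affiliations, and board certification") among the data collected, and the Introduction and section 2.4.3 both make it an aim to examine practitioner-related factors for adverse events (AEs).

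Section 2.5.2 names t-tests, rank-sum tests, and chi-square or Fisher tests between patients with and without AEs; of the rank tests it says that they "will be used to compare non-parametric continuous variables between the patient groups with AEs and those without". It adds Kaplan–Meier and Cox methods and sets a two-sided 5% level. Variables with p below 0.05 in the bivariate analysis, or judged clinically relevant, go into the final regression model.

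**The concern.** Patients treated by one practitioner share that person's technique, product preferences and, in part, case mix. That practitioner also has a share in ascertainment: after a blinded investigator has assessed symptoms, these are "subsequently confirmed for AEs by the practitioner who performed the TEA". If outcomes are correlated for these reasons, 332 patients carry less information than 332 independent observations.

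Two results are at stake. The first is the headline confidence interval, whose planned width is the whole justification for 350 patients. The second, and more important, is the practitioner-factor aim. Length of practice, affiliation and board certification are essentially constant across one practitioner's patients, so the effective sample for them is closer to the number of practitioners than to the number of patients. A patient-level test overstates the evidence. Because bivariate p-values also decide which variables enter the final model, the error carries forward. The Discussion expects the results to inform safer practice and guidelines, so a false signal about experience or certification would matter.

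**Working it through.** **Inputs from the article.** p = 0.12, d = 0.035, z = 1.96, dropout 5%, two-sided 5% tests (sections 2.5.1 and 2.5.2).

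**Inputs assumed, because the article does not give them.** Number of practitioners k = 10, 20 or 30, with equal caseloads; ICC 0.005 to 0.05.

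**Step 1: the plan's own figure.** n* = 0.12 × 0.88 × 1.96² / 0.035² = 331.16, and 331.16 / 0.95 = 348.6, so 349. Both stated figures reproduce.

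**Step 2: slack under independence.** Half-width = 1.96 × √(0.1056 / n). At n = 332 this is ±3.50 points; at n = 350 it is ±3.40. The design effect (DE) that still meets ±3.5 is n / 331.16, which is 1.003 at 332 and 1.057 at 350. Even with all 350 analysed, the tolerable ICC is 0.057 / (350/k − 1), about 0.0035 with 20 practitioners and 0.0017 with 10.

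**Step 3: margin with clustering at 332.** With m = 332/k, DE = 1 + (m − 1) × ICC and half-width = 1.96 × √(0.1056 × DE / 332). For example, with k = 20 and ICC 0.05: DE = 1 + 15.6 × 0.05 = 1.78 and half-width = 1.96 × √(0.1056 × 1.78 / 332) = 0.0466.

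**Step 4: actual size of a nominal 5% patient-level test** of a factor that is constant within practitioner: 2 × [1 − Φ(1.96 / √DE)]. In the same example, 1.96 / √1.78 = 1.47, giving 14.2%.

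| Practitioners (assumed) | Patients each | ICC (assumed) | DE | Half-width, points | Actual size of 5% test |
|---|---|---|---|---|---|
| 30 | 11.1 | 0.005 | 1.05 | ±3.6 | 5.6% |
| 20 | 16.6 | 0.01 | 1.16 | ±3.8 | 6.8% |
| 20 | 16.6 | 0.05 | 1.78 | ±4.7 | 14.2% |
| 10 | 33.2 | 0.01 | 1.32 | ±4.0 | 8.8% |
| 10 | 33.2 | 0.05 | 2.61 | ±5.6 | 22.5% |

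The size formula is a large-sample approximation. Unequal caseloads would raise the design effect further.

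**Step 5: dependence on incidence.** The margin also moves with p, even for independent patients. At an illustrative 20% it is 1.96 × √(0.20 × 0.80 / 332) = ±4.3 points.

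**The case against.** The strongest reply is that the article states neither an ICC nor a practitioner count, so the loss could be small. That stands. With 30 practitioners and ICC 0.005 the margin is ±3.6, which nobody would mind. A reader might infer that the stated precision is certainly missed, or that only a handful of practitioners take part. The article supports neither; it gives only the five sites.

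A second reply is that a condensed article may leave cluster terms to a full plan that is not shown, and that the examples in section 2.5.2 (sex, comorbidities, co-medications; demographics, materials, procedures) do not mention practitioner factors. This is fair as far as it goes: that those factors go through the named tests is an inference. But examining them is a stated aim, the named tests are the only ones offered for it, and the lists of examples are open-ended. The independence assumption in the sample size is printed in full and does not depend on any other document.

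Three stronger readings should be resisted:

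- **Sites as random clusters.** Treating the five sites this way would give much wider margins. If inference is confined to these sites as fixed strata, however, differences between them do not widen the interval: illustrative site rates of 4, 8, 12, 16 and 20% give about ±3.4 points.
- **The practitioner as sole ascertainer.** Section 2.4.2 puts a blinded assessment first, adds patient self-reporting, and describes the practitioner's step as a guard against omitted AEs.
- **Fault with calling 12% conservative.** The published rates in the Discussion sum to at most 9.83% + 1.27% = 11.1%, and 12% lies above that, in the direction that widens an absolute margin.

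Finally, this is a descriptive safety study with no decision threshold tied to ±3.5 points, so the precision statement alone is a modest matter. That is why the practitioner-factor analyses carry more weight here.

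**Conclusion.** The point holds in conditional form. The ±3.5-point margin is correct only for independent patients at about 12% incidence, and 332 evaluable patients leave no practical slack. For ICC 0.01 to 0.05 the interval would be about 0.3 to 1.2 points wider on each side with 20 practitioners (3.8 − 3.5 and 4.7 − 3.5), and 0.5 to 2.1 with 10 (4.0 − 3.5 and 5.6 − 3.5). Analysed with the tests as named, practitioner factors would be tested at 6.8% to 14.2% (20 practitioners) or 8.8% to 22.5% (10) instead of 5%.

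The direction needs only a positive within-practitioner correlation. The size rests on the assumed ICC, practitioner count and equal caseloads.

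**What to change.** 1. **Section 2.5.1.** State that ±3.5 points assumes independent patients and 12% incidence. Give the number of practitioners, or the expected range, and tabulate the margin over a range of ICC and incidence.
2. **Section 2.5.2, main interval.** Make sure that a practitioner identifier is recorded, and compute the main 95% confidence interval clustered on practitioner with a small-cluster correction.
3. **Section 2.5.2, models.** Fit the Cox and other regression models with a variance robust to practitioner clustering or a shared practitioner frailty. Test length of practice, affiliation and board certification on practitioner-level degrees of freedom, and do not select them by patient-level p-values. Do not stratify by site when estimating a factor that is constant within site, as affiliation may be, because its effect would then be inestimable.

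**Cost.** One identifier in the dataset, revised wording, wider intervals and less power for practitioner factors. With a t quantile on k − 1 degrees of freedom as the small-cluster correction, the margin for ICC 0.01 to 0.05 becomes ±4.0 to ±5.0 points with 20 practitioners and ±4.6 to ±6.5 with 10. At 12%, about 40 patients have an AE (0.12 × 332 = 39.8), so the models must stay small. No extra patients are needed.
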